### Variables

#### Outcome measures

##### Primary outcome measure

Self-reported 7-day point prevalence smoking abstinence, biochemically verified with expired carbon monoxide (CO) measures, is the primary outcome. Seven days of abstinence has been chosen as a consumption measure [41]. This variable will be recorded in every call of the intervention (48 h, 1 week, 15 days, and 1, 3, 6, and 12 months post discharge). Abstinent subjects at 1, 6, and 12 months in either of both groups (IG or CG) will be invited to attend a consultation at their hospital to verify their abstinence through the detection of exhaled carbon monoxide. The abstinence rate between the IG and the CG will be compared at 1, 6, and 12 months. In each call, nicotine withdrawal symptoms will be assessed according to the scale proposed by Hughes and Hatsukami [42].

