Over the last decade, some jurisdictions have implemented cost-effective measures, as proposed by the World Health Organization (WHO), to curb smoking among persons with mental disorders [20]. These measures are mainly policies for smoke-free areas, treatment to quit smoking, and community measures of sustained support to quit [22].

Hospitalization in smoke-free psychiatric centers increases the quality of life in both patients and professionals, and decreases the exposure to second-hand smoke [23]. In addition, such policies increase quit attempts by patients and their expectations of staying abstinent [24, 25]. Only total smoke-free areas completely protect patients from second-hand smoke [26]. In Spain, the tobacco control Law 42/2010 bans smoking in both indoors and outdoors areas of acute hospitals including psychiatric units. This legal framework, which implies abstinence of patients during hospitalization, creates a unique opportunity to promote smoking cessation among patients with mental disorders.

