Concerning treatment to quit smoking, the use of self-help materials, telephone advice, and psychological and pharmacological treatments have been shown to be effective [27, 28]. Although interventions to promote smoking cessation among patients with mental disorders aim to achieve abstinence, it is often necessary to first promote motivation to quit [27]. Thus, these patients would be able to make serious attempts to quit smoking when hospitals have trained professionals to respond to their needs and offer them pharmacological and psychological aids [29]. Interventions that combine pharmacological treatment and psychological therapy—primarily cognitive-behavioral psychological treatment—increase the likelihood of tobacco cessation in patients with mental disorders [30–32]. However, without patient monitoring after discharge, smoking is restored to previous levels in 2 weeks [33, 34]. Only a few clinical trials [21, 35, 36] have demonstrated the efficacy of multicomponent interventions (which included motivational, psychosocial, and pharmacological components) addressed to patients with mental disorders after discharge. In these studies, the intervention group showed higher abstinence rates, more quit attempts, and fewer cigarettes per day as compared to controls [21, 35, 36]. In addition, as shown in the general population, it is likely that patients with a mental disorder who quit smoking also reduce their levels of anxiety, increase their quality of life, and obtain better results in abstinence from other drugs [37].

In relation to community measures, “quitlines” (i.e., telephone counseling) stand out as an effective support in the general population [38]. However, this resource has so far been little used among populations with mental disorders [39]. The few studies conducted with mentally ill patients showed that a quitline intervention combined with nicotine replacement therapy (NRT) slightly but significantly increased 7-day point prevalence abstinence at 6 months follow-up, reduced the number of cigarettes consumed per day, and increased readiness to quit smoking [36, 39].

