**Fig. 1 Fig1:**
[figure not shown]
Study variables and collection time points. GHQ-12 12-item version of the General Health Questionnaire

The hypotheses of this study are the following:IG participants, as compared to CG participants, will demonstrate higher rates of biochemically verified 7-day point prevalence smoking abstinence, at all evaluation time points (48 h and 1, 6, and 12 months post discharge).IG participants, as compared to CG participants, will experience longer periods of sustained abstinence as demonstrated by sequential biochemically verified 7-day point prevalence smoking abstinence, at all evaluation time points.IG participants who continue to smoke, as compared to CG participants, will show greater reduction in the number of cigarettes smoked per day, at all evaluation time points.IG participants who continue to smoke, as compared to CG participants, will show an increase in the progression of their readiness to quit smoking, based on stages of change, at all evaluation time points.IG participants, as compared to CG participants, will have a higher level of self-efficacy to quit at all evaluation time points.

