#### Independent variables

Using a data collection form we will collect the following information:Sociodemographic data such as sex, age, occupation, and highest level of education attained.History and pattern of tobacco use, which will include information to obtain the Heavy Smoking Index as a measure of nicotine dependence self-reported by the participants [44, 45].General health data, such as self-perceived general health assessment by the question “how would you describe your health in a general way?”, and other medical conditions.Mental health data, such as diagnoses according to the DSM-5 groups of diagnostic criteria [46] and psychotropic treatment, will be obtained from participants’ clinical records by the researchers, whereas information about the number of emergency room visits, readmissions to psychiatric wards, and evaluation of mental distress measured using the 12-item version of the General Health Questionnaire (GHQ-12) [47, 48] will be self-reported by the participants.Variables of smoking cessation services reported by the participants, such as, if used, any other strategy for tobacco cessation, will be registered. It will also be recorded whether the patient has actively spoken with their psychiatrist, psychologist, nurse, or family doctor about their participation in the quitline, whether the professionals have agreed, and whether they have helped them, to assess the possible influence of these variables on the success (or failure) of the intervention.

Collected variables and their collection frequency are detailed in Fig. 1.

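### The primary outcome does not say how smoke-free days on a ward are scored, and the 48 h hypothesis counts days before discharge and randomization

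*Protocol article*

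**What the plan says.** - **Outcome rule (Variables, Primary outcome measure):** "Self-reported 7-day point prevalence smoking abstinence, biochemically verified with expired carbon monoxide (CO) measures, is the primary outcome". Self-reported abstainers at 1, 6 and 12 months "will be invited to attend a consultation at their hospital to verify their abstinence through the detection of exhaled carbon monoxide". The rule sets no condition on setting.
- **Ward setting (Background):** "the tobacco control Law 42/2010 bans smoking in both indoors and outdoors areas of acute hospitals including psychiatric units", a framework "which implies abstinence of patients during hospitalization". The Background adds that "without patient monitoring after discharge, smoking is restored to previous levels in 2 weeks".
- **Readmission:** The Independent variables section collects "readmissions to psychiatric wards" by self-report, and the Discussion lists rehospitalization as a covariate. Inpatient status otherwise appears only at entry, where discharge to another inpatient unit is an exclusion (Study population).
- **Timing of comparisons:** Hypothesis 1, at the end of the Background, claims higher biochemically verified 7-day abstinence "at all evaluation time points (48 h and 1, 6, and 12 months post discharge"). The Abstract and the end of the objectives list the same four times. The Primary outcome measure section compares arms, and offers CO testing, at 1, 6 and 12 months only.
- **Start of intervention (Procedure):** Allocation happens on the day of discharge. The 48 h call opens the quitline intervention outside hospital and collects post-discharge baseline data.

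**The concern.** By the protocol's own account, not smoking on the ward is enforced, and unmonitored patients are smoking as before within two weeks of discharge. A ward week is therefore weak evidence of quitting. CO testing cannot separate the two, because a person on a smoke-free ward really has not smoked. Using rehospitalization as a covariate does not repair the outcome: it is a post-randomization variable, and the score stays as it was.

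The control arm is the sensitive one. About 7 true abstainers are expected there, so a few false ones change the control rate and the odds ratio, which is the effect measure named under Data analysis. If readmission differed by arm, dilution would become bias.

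The 48 h comparison raises a related problem without any readmission. Most of its 7-day window lies before allocation, so the intervention cannot have influenced those days.

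**Working it through.** **Inputs from the protocol.** Abstinence at 12 months of 20% (IG) and 5% (CG), 20% loss, and 334 and 167 participants (Sample size and randomization). The Abstract and Design give 176 controls; 167 is used here.

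**Assumptions.** Those lost count as smokers. A share *r* of assessed non-abstainers has a 7-day window within a ward stay, is reached, reports abstinence and passes the CO test. The documents give no value for *r*; 1% to 3% is shown.

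**Base case.**
- IG: 0.80 × 20% = 16%. CG: 0.80 × 5% = 4%.
- Risk difference 12.0 points.
- OR = (0.16/0.84) / (0.04/0.96) = 4.57.
- True control abstainers: 167 × 0.04 = 6.7.

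**Who can be misread.** Only people who are assessed and not abstinent: CG 0.80 × 0.95 = 0.76 of the arm, IG 0.80 × 0.80 = 0.64. The 20% lost have no assessment to distort.

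**Formulas.** Recorded CG rate = 0.04 + 0.76*r*. Recorded IG rate = 0.16 + 0.64*r*. False control abstainers = 167 × 0.76 × *r*.

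| *r* (both arms) | IG | CG | Risk difference | OR | False CG abstainers |
|---|---|---|---|---|---|
| 0 | 16.0% | 4.0% | 12.0 points | 4.57 | 0 |
| 1% | 16.6% | 4.8% | 11.9 points | 3.99 | 1.3 |
| 2% | 17.3% | 5.5% | 11.8 points | 3.58 | 2.5 |
| 3% | 17.9% | 6.3% | 11.6 points | 3.26 | 3.8 |

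The number needed to treat moves from 1/0.120 = 8.3 to 1/0.1164 = 8.6 at *r* = 3%.

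**Power.** Among those followed up at 334:167 with 20% loss, power is about 99.3% at *r* = 0 and 97.3% at *r* = 3%.

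**Unequal readmission (illustration only).**
- *r* = 3% in CG and 1% in IG: 16.64% v 6.28%, a difference of 10.4 points.
- *r* = 1% in CG and 3% in IG: 17.92% v 4.76%, a difference of 13.2 points.
- The base is 12.0 points, so the error can go either way.

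**48 h.** A 7-day window ending 48 h after discharge holds 7 − 2 = 5 days before discharge. Allocation is on the day of discharge, so these days precede randomization. They are all ward days for stays of at least five days. No CO test is planned at this call, so the verification that hypothesis 1 requires is not available.

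**The case against.** The best defence is that the outcome measures consumption: a person who did not smoke for seven days is correctly recorded as not having smoked, and what abstinence should mean is a choice of estimand. That stands in part. It is also why scoring every inpatient as not abstinent would be wrong, since it would turn a true quitter who is readmitted into a smoker. But the trial wants to conclude about quitting after discharge, and its own text treats ward abstinence as enforced and short-lived.

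The protocol never says how an inpatient at a follow-up call is handled, and a rule may exist in the full protocol or analysis plan. That limits the point to the outcome rule as printed. It does not cover the 48 h hypothesis, which is stated expressly. Sequential and continuous abstinence give some protection, because a single readmission at one assessment cannot produce them.

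Three stronger readings are tempting and not supported:
- A reader might infer that readmitted participants in general are recorded as abstinent. Someone admitted three days earlier who smoked before admission fails the rule, as does someone who smoked after leaving, was not reached, or was not verified.
- A reader might infer that the 48 h window consists of ward days for everyone. The Study population section admits stays of just over 24 h.
- A reader might infer that the trial is biased between arms or loses its power. Nothing in the documents says the intervention changes readmission, and with equal shares the risk difference and power barely move.

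**Conclusion.** The point holds in a limited form. As printed, the rule lets a participant whose 7-day window at 1, 6 or 12 months falls within a stay on a smoke-free ward count as a verified abstainer without having quit.

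At an assumed 1% to 3% of assessed non-abstainers, equal in both arms and with those lost counted as smokers, the harm is to the odds ratio and the control rate, and it runs toward the null. The risk difference, number needed to treat and power are little affected. The size rests entirely on the assumed share and on every affected person being reached and verified. Bias between arms would need readmission to differ by arm.

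The 48 h part rests on no assumed rate. A verified 7-day comparison at that call cannot test the intervention: about five of the seven days come before allocation, no CO test is planned, and the call is itself the intervention's starting point.

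**What to change.** 1. At each assessment, ask whether any of the last seven days were spent in a smoke-free inpatient unit, and record the dates.
2. If so, repeat the assessment and CO test once seven days have passed since discharge, within the visit window. Where that is not possible, keep the score under the Primary outcome measure section and add a sensitivity analysis that excludes or rescores these participants. Do not count them automatically as not abstinent.
3. Remove 48 h from the verified 7-day claim in hypothesis 1 and, for this outcome, from the comparison times in the Abstract and the objectives. Report it descriptively as no smoking since discharge.

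The cost is one extra question at calls already planned, a later call and CO test for a few participants, and a short edit to the text.

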##### Secondary outcome measure

We will also record other smoking variables such as continuous abstinence. Moreover, for nonabstinent patients we will ask about their tobacco use (quantity), type of tobacco consumed (cigarette/cigar/other), number of quit attempts, and other variables included in the “smoking” section in Fig. 1. Moreover, using an ad-hoc Likert scale from 0 to 10 we will evaluate the level of self-efficacy to quit or reduce consumption, the intention to quit, and the intention to reduce consumption. The individual’s willingness to quit will be also evaluated according to the Prochaska and Di Clemente Stages of Change model, which measures four stages of readiness to quit smoking (precontemplation, contemplation, action, and maintenance) [43].

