**Methods:**

A pragmatic randomized controlled trial, single blinded, will include 2:1 allocation to the intervention group (IG) and the control group (CG). The IG will receive telephone assistance to quit smoking (including psychological and psychoeducational support, and pharmacological treatment advice if required) proactively for 12 months, and the CG will receive only brief advice after discharge. The sample size, calculated with an expected difference of 15 points on smoking abstinence between groups (IG, 20% and CG, 5%), α = 0.05, β = 0.10, and 20% loss, will be 334 participants (IG) and 176 participants (CG). Participants are adult smokers discharged from psychiatric units of five acute hospitals.

Measurements include dependent variables (self-reported 7-day point prevalence smoking abstinence (carbon monoxide verified), duration of abstinence, number of quit attempts, motivation, and self-efficacy to quit) and independent variables (age, sex, and psychiatric diagnoses). In data analysis, IG and CG data will be compared at 48 h and 1, 6, and 12 months post discharge. Multivariate logistic regression (odds ratio; 95% confidence interval) of dependent variables adjusted for potential confounding variables will be performed. The number needed to treat to achieve one abstinence outcome will be calculated. We will compare the abstinence rate of enrolled patients between groups.

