In Catalonia, the health information and care telephone line “061 CatSalut Respon” provides a free support program to quit smoking, which acts as a quitline. A nursing team, experts in telephone assistance and smoking cessation, provide an individualized intervention to quit smoking through intensive care for 1 year. However, this service has not so far been used for patients with mental disorders. Quitlines may have some advantages over other cessation services, as they can increase access, are less costly than face-to-face visits [38], and offer a solution to the lack of systematic interventions in patients with mental disorders especially after discharge [34, 40]. However, contact with the quitline is usually initiated by the smoker, and is not usually initiated proactively by the treatment provider. Therefore, we propose a pragmatic randomized controlled trial that uses the existing resources of 061 CatSalut Respon to engage patients with mental disorders identified during hospitalization in acute psychiatric hospital units.

The aim of this study is to assess the effectiveness of a telephone-based (quitline) intervention for smoking cessation addressed to smokers with severe mental disorders after discharge from adult inpatient acute units (the 061 QuitMental study). The intervention group (IG) will receive a telephone intervention to quit smoking (including psychological and psychoeducational support and pharmacological treatment advice, if required) proactively for 12 months, and the control group (CG) will receive only brief counseling after discharge.

The specific objectives of the 061 QuitMental study are as follows:to assess the effectiveness of the intervention in relation to the characteristics of the smokers (mental disorder, comorbidity, age, sex, and educational level and occupation);to compare the levels of motivation to quit smoking, self-efficacy, attempts to quit smoking, and the likelihood of smoking abstinence in the intervention group and the control group;to describe the use and satisfaction with the quitline in the intervention group and the control group; andto assess the feasibility of this intervention to systematically offer it at a community level.

These objectives will be analyzed by comparing the results obtained from the IG and the CG at several time points post discharge: 48 h and 1, 6, and 12 months (Fig. 1).

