### Data analysis

The abstinence prevalence will be analyzed by groups taking into account sociodemographic determinants. Logistic regression analysis will be used to assess the effectiveness of the intervention (OR and 95% confidence interval) with regard to the CG, using the different dependent variables previously described (abstinence, reduction of the number of cigarettes, motivation, etc.). Thus, the IG and the CG will be compared in different moments of the follow-up. In addition to randomization, to warrant comparability, we will fit multivariate logistic models to adjust for potential confounding variables. All analyses will be carried out by “intention to treat”, to take into account possible losses during follow-up. We will also analyze resource use, such as the number of calls, satisfaction with the quitline, and type of treatment offered, among others.

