## Discussion

Smoking has serious implications for people with severe mental illnesses, mainly in terms of quality of life and mortality but also in economic costs and marginalization. Hospital mental health units are an optimal setting to intervene and promote patient engagement in tobacco cessation treatment [21]. For this reason, it is necessary to offer and improve a variety of interventions to motivate and promote cessation among these patients.

Patients with mental health disorders are usually excluded from smoking cessation trials [20], and consequently there is scarce evidence for the effectiveness of quitlines in this population. As these patients usually have high comorbidity and high smoking dependence, they represent a complex population for smoking cessation intervention. They need more intensive counseling, pharmacological intervention, and longer follow-up support to achieve cessation [20], so there is a need to tailor these strategies to this population [50]. Only a few studies of quitline effectiveness have included mental health patients and, usually, quitline interventions have not been tailored to this population [51]. This is the first randomized trial to test a quitline intervention specifically tailored to the needs of mental health patients that incorporates a long-term follow-up of 1 year, since other studies have performed follow-up periods from 6 to 7 months [52] and with smaller samples [53].

The large sample, together with the long follow-up period, will allow us to perform other subgroup analyses in addition to assessing smoking cessation. The main expected outcome is an increased rate of CO-verified 7-day point prevalence abstinence in the intervention group, as compared with the control group. All smokers, regardless of their level of motivation to quit, will be eligible to participate. Analyses will consider covariates such as psychiatric diagnoses, use of other psychoactive substances, psychological distress, mental illness relapse and rehospitalization, and sociodemographic variables. Other relevant outcomes for comparison will include the level of motivation to quit, number of quit attempts, and level of psychological distress.

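### The number of quit attempts is asked only of patients still smoking at a call but compared between whole arms, which biases the comparison against the intervention

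*Protocol article*

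**What the plan says.** The section on the secondary outcome measure defines who is asked: "for nonabstinent patients we will ask about their tobacco use (quantity), type of tobacco consumed (cigarette/cigar/other), number of quit attempts". Quantity and type of tobacco stand in the same list.

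Three other places use quit attempts as an outcome of the arms as randomized:

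- The abstract, under Methods, lists among the dependent variables "duration of abstinence, number of quit attempts, motivation, and self-efficacy to quit".
- The specific objectives at the end of the Background include "to compare the levels of motivation to quit smoking, self-efficacy, attempts to quit smoking, and the likelihood of smoking abstinence in the intervention group", with controls as the comparator.
- The Discussion states: "Other relevant outcomes for comparison will include the level of motivation to quit, number of quit attempts, and level of psychological distress".

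None of the three limits the comparison to patients who still smoke. The hypotheses, printed after Fig. 1, do state such a limit for cigarettes per day: "IG participants who continue to smoke, as compared to CG participants, will show greater reduction in the number of cigarettes smoked per day". They do the same for readiness to quit. No hypothesis concerns quit attempts.

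The Data analysis section adds: "All analyses will be carried out by “intention to treat”, to take into account possible losses during follow-up". It names logistic regression with odds ratios as the method for the dependent variables.

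**The concern.** Quantity and type of tobacco apply only to people who smoke. Quit attempts do not: someone who is abstinent after discharge has made at least one. Asking only nonabstinent patients conditions the comparison on a status reached after randomization, and the trial is built on the expectation that this status differs between arms. The patients left out are those whose attempt succeeded, and the plan expects proportionally more of them in the intervention arm.

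Intention to treat cannot repair this, because the excluded patients are in follow-up and simply have no value at that call. At stake is a named specific objective. The trial could report little or no effect of the quitline on quit attempts when there is one, and the better the quitline works, the larger the distortion.

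**Working it through.** The documents state no figure for quit attempts, so there is none to reproduce. The check takes the protocol's planned rates and adds assumed attempt rates over a range.

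**Inputs from the protocol (Sample size and randomization).** Abstinence at 12 months q = 0.20 (intervention) and 0.05 (control); 334 and 167 patients; 20% loss to follow-up. The abstract and Design section give 176 controls; both figures are shown.

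**Step 1: patients with no value at the 12-month call because they are abstinent.**

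- Intervention: 0.20 × 334 = 66.8, about 67.
- Control: 0.05 × 167 = 8.35, about 8 (with 176 controls, 8.8).
- After 20% loss (267 and 134 patients): 53.4 and 6.7, about 53 and 7.

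The share missing for this reason is 0.20/0.05 = 4 times higher in the intervention arm.

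**Step 2: what the patients asked would show.** Let A be the true share with at least one attempt (assumed, not in the documents), and count every abstainer as an attempter. Among those asked, the observed share is (A − q)/(1 − q). The share of attempters lost is q/A.

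Equal true rates in both arms:

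| A | Seen, intervention | Seen, control | Difference (points) | Attempters lost, intervention / control |
|---|---|---|---|---|
| 30% | 12.5% | 26.3% | −13.8 | 67% / 17% |
| 40% | 25.0% | 36.8% | −11.8 | 50% / 12.5% |
| 50% | 37.5% | 47.4% | −9.9 | 40% / 10% |
| 60% | 50.0% | 57.9% | −7.9 | 33% / 8% |
| 70% | 62.5% | 68.4% | −5.9 | 29% / 7% |

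The true odds ratio is 1 in every row; the observed one runs from 0.40 (A = 30%) to 0.77 (A = 70%).

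A true advantage for the intervention:

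| True rates | True difference | Seen | Observed difference |
|---|---|---|---|
| 40% v 30% | +10 | 25.0% v 26.3% | −1.3 |
| 45% v 30% | +15 | 31.3% v 26.3% | +4.9 |
| 50% v 40% | +10 | 37.5% v 36.8% | +0.7 |
| 60% v 50% | +10 | 50.0% v 47.4% | +2.6 |
| 50% v 30% | +20 | 37.5% v 26.3% | +11.2 |

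For 50% v 40%, the odds ratio falls from 1.50 to 1.03.

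**Step 3: where the sign changes.** The observed difference is zero when the intervention rate equals 0.20 + 0.80 × (control rate − 0.05)/0.95. With 30% in control this is 0.20 + 0.80 × 0.263 = 41.1%, and with 40% it is 0.20 + 0.80 × 0.368 = 49.5%. A smaller true advantage reverses; a larger one shrinks but keeps its sign.

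**Step 4: the mean number of attempts.** If abstainers average m1 attempts and nonabstinent patients m0, restricting the question lowers an arm's mean by q × (m1 − m0): 0.20 × (m1 − m0) in the intervention arm and 0.05 × (m1 − m0) in control, taking m1 and m0 as alike in both arms. The documents give neither mean, so no size can be stated. The bias runs against the intervention when abstainers average more attempts than nonabstinent patients.

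**The case against.** The strongest reply is that an analyst can code every abstinent patient as having made at least one attempt. Smoking status is recorded at the calls, so this restores the any-attempt proportion (40% v 30% in the first unequal example) with no new question. That stands. A reader might infer that the data are beyond recovery, and for an any-attempt indicator they are not. But the abstract, the secondary outcome section and the Discussion name the number of attempts, and that count cannot be rebuilt for abstainers.

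Other parts of the reply also stand:

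- A reader might infer that abstainers are never asked. The restriction applies call by call, so a patient abstinent at 12 months who smoked at 1 or 6 months is asked at the earlier call. The later, successful attempt still goes uncounted.
- A reader might infer that the intervention arm loses most of its attempters. A majority is lost only if fewer than 40% of that arm attempt, and the documents give no such rate. Only a larger share than in control is supported.
- A reader might infer that the result would change sign. That depends on assumed rates: 45% v 30% leaves +4.9 points.

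It can also be said that Fig. 1 and the call script are not shown, and that one condensed sentence may not describe the full instrument. The article refers to Fig. 1 for the variables and how often they are collected. The secondary outcome section says explicitly who is asked, and nothing visible overrides it. A reading confined to continuing smokers is possible, but the article states that limit for other outcomes and not for this one.

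**Conclusion.** The concern holds. The collection rule for quit attempts does not match the comparison that the objectives, abstract and Discussion promise, nor the statement that every analysis is by intention to treat. At the protocol's own abstinence rates, about 67 intervention and 8 control patients have no value at the 12-month call because they succeeded.

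For the share with any attempt, the bias is against the intervention at every assumed rate examined: 13.8 to 5.9 points when true rates are equal at 30% to 70%, and a true +10 reduced to between −1.3 and +2.6. Attenuation is expected; reversal is possible but not certain. These sizes assume that the planned 20% and 5% occur, that each abstainer counts as an attempter, and that attempts are compared only among those asked at that call.

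The outcome is secondary, and neither the primary outcome nor the sample size depends on it. The change should still be made, because it affects a stated objective and costs very little.

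**What to change.** In the secondary outcome section, take the number of quit attempts out of the list reserved for nonabstinent patients. At the 1, 6 and 12 month calls, which both arms share, ask every participant how many attempts they have made since the previous common assessment, whatever their current smoking status. Count the attempt behind current abstinence, and say how one that spans two assessments is counted so that both arms are handled alike. Compare all randomized participants.

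For data already collected under the present rule, code abstinent patients as having made at least one attempt and compare the any-attempt proportion. If the sponsor does mean continuing smokers only, the objectives, abstract and Discussion should say so and state that this is not a randomized comparison.

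The cost is one question moved, one change of wording, and a few seconds per call with abstinent participants.
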